#### Cognitive or Emotional Measures

A dynamic model of smoking relapse is the organizing framework guiding the overall intervention and evaluation approach [14]. Selected measures evaluate possible factors in “cessation fatigue,” a latent construct proposed to contribute to “relapse proneness” and operationalized by declines in motivation, expectancy for success, coping attempts, self-efficacy, and self-control resources [14]. To explore the concept of “cessation fatigue” [16], the following patient-reported outcome measures are collected at baseline, 3, 6, 9, and 12 months post study enrollment: cessation fatigue [17], Abstinence Related Motivational Engagement – Short Form [40], smoker versus quitter identity [41], smoker group identity [41], residual attraction and vulnerability to smoking [42], situational smoking abstinence self-efficacy [43], Proactive Coping Inventory [44,45]; and Patient Health Questionnaire-4 for anxiety and depression [46-48] (see Table 1).

#### Biochemical Confirmation of Abstinence

Participants who self-report abstinence on 6- and 12-month surveys are mailed a kit for self-collection of the dried blood spot. Participants are trained on self-collection of dried blood spots using an online video and instructional booklet [49]. Dried blood spot samples will be analyzed for cotinine to confirm self-report, following previously validated approaches [50] (Table 1).

### Measures and Data Collection for Embedded Mixed Methods Personal Network Study

#### Overview

Personal network recruitment, screening, and inclusion and exclusion criteria are the same as for the main study. All main study participants (egos) complete two online personal network assessments, one at baseline and the other at 12 months post baseline. Personal network assessment questions address network composition and structure and are administered using REDCap (Research Electronic Data Capture; Vanderbilt University) [51-54]. Each participant (ego) is asked to name 25 individuals (alters) with whom they have had any kind of contact over the past six months [55,56]. Egos are then asked questions about each alter to capture the compositional variables, such as the proportion of individuals who smoke in their personal network and the social support and influence for abstinence. Personal network structure is defined by asking the participant (ego) whether each unique pair of alters talks to each other independently of ego [52].

#### Alter Surveys

We use respondent-driven sampling [57-62] to survey smoking alters who receive a helping conversation from the ego to measure the spread of smoking cessation information and behaviors. With each weekly (months 1‐6) or biweekly (months 7‐12) period, egos also receive a text message link to an anonymous online survey (alter survey) that can be passed on to alters for completion. Alter surveys query smoking status, reaction to the helping conversation, context and content of the helping conversation, and if the alter has shared helping conversation information with others in their own personal network.

#### Personal Network Qualitative Interviews

A subsample (n=60) was selected for qualitative interviews about relapse or abstinence and the qualitative aspects of personal network continuity or change [63,64], interactions with members of personal network, exchange of information, assistance, or goods related to smoking cessation. Participants who had completed at least 5 months of the study were selected in 30 dyads (a dyad is one relapser paired with a like abstainer or maintainer from the same study arm, matched on gender). The 15 relapser or maintainer dyads from each arm are matched on the approximate number of weeks participating in the study. Network visualizations on connectedness, alter centrality, closeness, interaction, demographics, and smoking status are generated using the R software (R Foundation for Statistical Computing) package *ggraph* and shown to participants to facilitate discussion in qualitative interviews.

### Sample Size, Power Estimates, and Analysis

#### Power and Sample Size for Pragmatic Randomized Controlled Trial (pRCT)

A sample size of 940 participants would yield 80% power to detect a difference in smoking cessation rates between arms of 10%, assuming a conservative control arm rate of 0.25 [65], 30% dropout, and a noncontinuity corrected *χ*^2^ test. This difference is smaller than that found in the preceding pilot feasibility study (difference=46%); this effect size was chosen as a clinically significant difference with public health implications and is feasible, given the pilot results. This sample size also yields 90% power to detect standardized effect sizes for continuous secondary outcomes of Cohen *d*=0.26, a small-to-medium effect size, and considered to be a good estimate for a minimum important difference for patient-reported outcomes.

#### Personal Network Study Sample Size

To measure change in personal networks at two times, 940 participants (470 in each arm) will be sufficient. Although there are few longitudinal personal network studies among those with substance use disorders or those who have recently quit using as models [55], studies using dynamic network analyses to estimate the impact of life events on an individual’s social context typically include between 33‐250 participants [66-72]. Informed by the previous feasibility study, the present personal network study features an increased sample size, a lengthened interval between the first and second personal network assessment to 1 year, and broadened the personal network name generator question to capture both strong ties and weak ties. The qualitative sample (n=60) is theory-driven; sufficient for coverage of basic consensus and range of variability of critical themes [73].

#### Analytic Plan

##### General Quantitative Approaches

For this pRCT, descriptive statistics (mean, SD, and frequencies) will be computed for baseline participant characteristics. Participant-level covariates will be screened in bivariate analyses and included in multivariate analysis if they are related to the outcome at *P*<.2, are associated with dropout, or used in the randomization procedure. Before beginning the analyses described below to address study hypotheses, we will compare baseline characteristics of participants who drop out to participants with complete data to assess the missingness mechanism (missing completely at random [MCAR], missing at random [MAR], and missing not at random [MNAR]) and generalizability of our results [74-76]. If missingness is ignorable (MCAR and MAR), we will use likelihood-based methods that use all available data, adjusting for covariates that are associated with dropout. If missingness is nonignorable, we will use pattern mixture models. Sensitivity analyses with multiple imputation will be undertaken if missing data rates for the primary outcome are greater than 10% at any follow-up time used in the analysis.

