### Research Objectives

This study is designed to assess the effect of Helpers Stay Quit training on the proportion and duration of participants maintaining abstinence or relapsing over time and on participants’ personal network structure and interactions related to smoking and smoking cessation. Primary and secondary research questions are as described in study-specific aims (Textbox 1).

Textbox 1.The Helpers Stay Quit study-specific aims.Aim 1: Using a 2-group, pragmatic randomized, controlled trial (pRCT; N=940) in which abstinent smokers (2-6 weeks abstinent) are randomized to the Helpers Stay Quit intervention or quitline follow-up usual care, to evaluate the effectiveness of Helpers Stay Quit on:Smoking status (30-day and 7-day point prevalence abstinence) at 6- and 12-month intervals (primary outcome).The number, timing, and duration of participants’ lapses and relapses to smoking (secondary outcome).Rates of participants’ self-reported delivery of helping conversations to other tobacco users (secondary outcome).Aim 2: embed a mixed methods social network study into the pRCT to examine the Helpers Stay Quit effects on:Composition and structure of participants’ personal networks.Characteristics of participants’ personal networks over the course of the study (eg, proportion of smokers in personal network).Spread of smoking cessation-related information, assistance, and behaviors from participants to others in their personal networks.Recipients of helping conversations report about smoking-related interactions and information exchange with participants and associated cessation-related behavior change.Aim 3: using personal network metrics derived from the personal network study (eg, size, composition, and structure), conduct mediational analyses of personal network effects on the primary and secondary study outcomes in Aim 1.

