##### Eligibility Criteria

The eligibility criteria are shown in Textbox 2.

Textbox 2.Eligibility criteria.Inclusion criteria:Participants are aged 18 years and older.Abstinent from smoking for between 14 and 60 days per self-report.Primary tobacco use is cigarettes.Has access to the internet via computer or mobile device.Self-described proficiency with English.Willing and able to send and receive weekly text messages using personal mobile phone.Will allow the quitline to share its client data with the research team.Willing to complete online surveys at baseline, 3, 6, 9, and 12 months.Willing to self-collect dried blood spot for biological confirmation of smoking status and send back to the research team.If assigned to the Helpers Stay Quit condition, willing to complete the training within 14 days.If selected, willing to participate in a qualitative interview.Willing to forego any other training for tobacco cessation intervention or support (ie, to become a cessation counselor or facilitator or support person, eg, “quit buddy”) for the duration of their study enrollment.Exclusion criteria:Any previous exposure to Helpers Stay Quit or other cessation training in the previous 2 years.Relapse within 10 days (run-in phase) before enrollment and randomization.Participants are not precluded from continuing their personal tobacco cessation activities with quitline or other services or aids (eg, support groups, medication, etc).Concomitant use of cessation aids is tracked while participants are enrolled in the study via online surveys (baseline, 3, 6, 9, and 12 months, and weekly or biweekly text surveys).

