##### Aim 1: Abstinence and Relapse

Abstinence rates at 6- and 12-months postrandomization and biochemically confirmed abstinence at 6- and 12-months postrandomization will be compared between arms using multivariable logistic regression for each outcome (6- or 12-months). Independent variables will include intervention status, strata (race and ethnicity), quitline, and covariates (as described above). We will compare time to first relapse using Cox models and Kaplan-Meier curves. The number of relapses and helping conversations will be compared between study arms using Poisson regression, with the zero-inflated Poisson or negative binomial model used if appropriate. We will carry out secondary analyses using general linear mixed models to examine change in cognitive and emotional measures of participant-reported outcomes (described above in the General Quantitative Approaches section) for participants randomized to receive Helpers Stay Quit compared to participants randomized to the usual care arm.

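### Covariates for the primary abstinence models are chosen by a P<.2 screen against each outcome, so the adjustment set is not fixed in advance and may differ between models; length of abstinence at entry is also described in two ways

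*Protocol article*

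**What the plan says.** General Quantitative Approaches gives three routes by which a covariate enters the multivariable models. The first is outcome-based: "Participant-level covariates will be screened in bivariate analyses and included in multivariate analysis if they are related to the outcome at" P<.2. The others are association with dropout and use in the randomisation.

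Aim 1: Abstinence and Relapse applies this to one logistic regression per outcome: "Independent variables will include intervention status, strata (race and ethnicity), quitline, and covariates (as described above"). Textbox 1 lists 30-day and 7-day point prevalence abstinence at 6 and 12 months as primary. Aim 1 adds biochemically confirmed abstinence at both times.

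The Randomization section stratifies by quitline and by race/ethnicity only. Length of abstinence at entry is neither a stratifier nor a named model term. It is described in two ways. Aim 1 in Textbox 1 speaks of a trial "in which abstinent smokers (2-6 weeks abstinent) are randomized"; Textbox 2 requires "Abstinent from smoking for between 14 and 60 days per self-report". The run-in section allows up to 10 days for baseline measures between screening and randomisation.

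**The concern.** A primary model should be settled before anyone sees how the outcome relates to the candidate covariates. Here the rule is stated in advance, but its result is not: the covariates come from the same outcome data that yield the treatment effect, and each outcome runs its own screen.

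This affects interpretation because an odds ratio is non-collapsible. Adding a prognostic covariate changes the quantity being estimated even under perfect randomisation. Two abstinence models with different covariates may therefore target different conditional odds ratios. None of them corresponds directly to the planning target, which is a difference in proportions with an unadjusted test.

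The two descriptions of abstinence length raise a separate matter: a reader cannot tell from the article which population was randomised.

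**Working it through.** **1. Reproduce the planning figure.** The power section states "A sample size of 940 participants would yield 80% power to detect a difference in smoking cessation rates between arms of 10" percentage points, "assuming a conservative control arm rate of 0.25", and "30% dropout, and a noncontinuity corrected" chi-square test. Two-sided alpha of 0.05 is assumed, as the article does not state it.

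n per arm = [1.96 × √(2 × 0.30 × 0.70) + 0.8416 × √(0.25 × 0.75 + 0.35 × 0.65)]² / 0.10² = [1.270 + 0.542]² / 0.01 ≈ 328.5, so 329.

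Total = 658 / 0.70 = 940, which matches the article ("940 participants (470 in each arm) will be sufficient" in the personal network section). Power at 329 per arm is 0.801. The covariate rule does not affect N.

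**2. What the odds ratio means.** The design effect is a marginal odds ratio of (0.35/0.65) / (0.25/0.75) = 1.62. The table shows the conditional odds ratio for the same 25% versus 35%, by the assumed SD of the covariates' linear predictor.

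| Assumed SD | Conditional OR |
|---|---|
| 0 | 1.62 |
| 0.5 | 1.65 |
| 0.8 | 1.71 |
| 1.0 | 1.77 |
| 1.5 | 1.93 |

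**3. Behaviour of the screen.** The simulation used 658 evaluable participants, 12 candidate covariates and 2,000 runs per scenario. The control rate was 25% and the conditional odds ratio 1.615, or 1 under the null. Covariate strengths are assumed, as log-OR per SD.

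| Scenario | Type I error, screen | Power, screen | Power, all 12 | Power, fixed 3 | Median OR: none / screen / all 12 |
|---|---|---|---|---|---|
| 12 null | 4.65% | 78.7% | 78.6% | 78.7% | 1.61 / 1.61 / 1.62 |
| 3 at 0.4, 9 null | 5.0% | 75.7% | 75.9% | 75.8% | 1.55 / 1.62 / 1.64 |
| 3 at 0.2, 9 null | 4.95% | 78.6% | 79.4% | 79.7% | 1.60 / 1.62 / 1.63 |
| 12 at 0.15 | 5.3% | 77.1% | 77.6% | 76.1% | 1.58 / 1.62 / 1.63 |

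The Monte Carlo standard error at 5% is √(0.05 × 0.95 / 2000) ≈ 0.5 points, so no inflation is visible. Screened and fixed lists differ in power by about one point at most, in either direction.

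The selected sets differed between two equally predicted outcomes in 97% to 99.9% of runs. A null covariate entered about 20% of the time. A modest predictor (log-OR 0.15 to 0.20) was missed in about 16% to 37% of runs. The two outcomes were generated independently given arm and covariates. Real 6- and 12-month, or 30-day and 7-day, outcomes in the same people are correlated, so their sets would agree more often than this.

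**4. A second simulation.** It used 400 trials, 329 per arm and 20 candidates, 4 of them prognostic at log-odds 0.6, with arm log-odds 0.48. The screen kept 4 to 12 variables.

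| Model | Mean OR | Power |
|---|---|---|
| Unadjusted | 1.48 | 65.5% |
| Screened | 1.65 | 74.0% |
| Pre-specified | 1.64 | 75.0% |

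The Monte Carlo standard error of power is √(0.75 × 0.25 / 400) ≈ 2.2 points, so 74.0% versus 75.0% is no detectable difference. Null rejection over 600 runs was 5.8% unadjusted, 5.0% pre-specified and 5.8% screened, with a standard error of about 0.9 points.

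**5. Length of abstinence.** Six weeks is 42 days, whereas 60 days is 60/7 = 8.6 weeks. If the 60-day limit applies at screening, which the article does not say, a 10-day run-in gives up to 70 days, or 10 weeks. If days abstinent were uniform over 14-60 (assumed), the SD is 46/√12 = 13.3. The 95% range of chance imbalance at 470 per arm is then 1.96 × 13.3 × √(2/470) ≈ ±1.7 days.

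**The case against.** The strongest reply is that the rule is pre-stated, that it looks at covariate and outcome rather than at arm, and that it costs almost nothing in error rate or power. The working above bears this out. The candidate list and effect measure may also sit in an analysis plan that is not shown. That answers a complaint about a missing list. It does not answer a complaint about the rule, because the article fixes outcome-based selection and its closing section says results will follow the analytic plans it describes.

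A reader might infer more than the documents support:

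- **That the screen inflates type I error.** Neither simulation shows this.
- **That a fixed list would raise power from about 66% to 75%.** That contrast is with an unadjusted model, which Aim 1 does not plan. The 66% also arises because the design's marginal effect was imposed as a conditional one, shrinking the risk gap to about 8 points (control rate 25%, strengths per SD). At the design effect, unadjusted power is 80%.
- **That abstinence length is left to chance.** It can enter through the screen. A covariate with log-OR 0.3 per SD passes about 98% of the time, and one at 0.4 almost always. Entry is not guaranteed, but a strong predictor would rarely be lost.
- **That a fixed list makes the 6- and 12-month odds ratios fully comparable.** The same covariates can predict the two outcomes with different strength, and step 2 shows that this alone moves the conditional odds ratio.
- **That one abstinence window is the one actually used.** The article reports no enrolled distribution, so it does not show which description is accurate.

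**Conclusion.** The concern holds as one of pre-specification. Beyond quitline and race/ethnicity, the primary models' covariates depend partly on each outcome's own data and may differ across the abstinence models, so each conditional odds ratio may target a somewhat different quantity. The numerical consequence is small unless covariates are strongly prognostic. Median odds ratios under the screen were within about 0.02 of those with all 12 covariates, power was within about one point of a fixed list, and N = 940 is unaffected. These sizes rest on assumed numbers and strengths of covariates, which the article does not give.

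The change is worth making because it is cheap and closes off a route by which outcome data can shape the primary model. The conflict between 2-6 weeks and 14-60 days is real and needs reconciling.

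**What to change.** Before outcome data are examined:

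1. Replace the P<.2 outcome screen with one fixed covariate list used in every abstinence model: quitline, race/ethnicity, self-reported length of abstinence at entry, and a few prognostic baseline variables. Candidates are time to first cigarette and cessation-medication use from the quitline data, and baseline self-efficacy from Table 1. Confirm that abstinence at entry was stored in days, and take medication use as recorded before randomisation.
2. Keep dropout-associated covariates in the primary likelihood-based missing-data approach as planned, or move them to a stated sensitivity analysis. Moving them only into an imputation model would conflict with the plan, which uses multiple imputation as a sensitivity analysis.
3. Report a standardised risk difference with the odds ratio, to match the 10-point planning target.
4. Reconcile Textbox 1, Textbox 2 and the run-in section on length of abstinence, and state the time at which the limit applies.

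The cost is wording and the discipline of locking the list. The downside is that a predictor outside the list is not used. Timing matters: enrolment is complete, and 337 participants had finished 12-month surveys by August 31, 2025.

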## Results

This trial was funded in 2021 and is currently ongoing. Initial study start-up was delayed when the first author, MM, moved to the University of Colorado. Recruitment began in December 2022, and we completed enrollment and randomization of 940 participants on September 15, 2025. As of August 31, 2025, when the paper was submitted, 337 participants (65%) had completed the study with the 12-month follow-up surveys.

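### A baseline comparison of dropouts with completers decides whether missingness is ignorable, which it cannot show, so no MNAR check on the primary outcome is assured

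*Protocol article*

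**What the plan says.** Under General Quantitative Approaches, before the main analyses, the team will "compare baseline characteristics of participants who drop out to participants with complete data to assess the missingness mechanism", with MCAR, MAR and MNAR listed as the possible findings. The finding then selects the method. If missingness is ignorable, likelihood-based methods use all available data, adjusted for covariates associated with dropout. Otherwise: "If missingness is nonignorable, we will use pattern mixture models". A further rule reads "Sensitivity analyses with multiple imputation will be undertaken if missing data rates for the primary outcome are greater than 10" per cent at any follow-up time analysed.

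Under Aim 1: Abstinence and Relapse, abstinence is compared between arms "using multivariable logistic regression for each outcome (6- or 12-months"). The power section plans for 940 participants, "assuming a conservative control arm rate of 0.25 [65], 30% dropout, and a noncontinuity corrected" chi-square test.

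**The concern.** The three mechanisms differ in what missingness depends on: nothing (MCAR), observed data (MAR), or the missing value itself after allowing for observed data (MNAR). A baseline comparison looks only at observed data. It can give evidence against MCAR. It carries no information on whether, among people with the same baseline profile, those who went back to smoking were less likely to answer.

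That is the pattern to fear in a relapse-prevention trial. It would distort the arm comparison if it were stronger in one arm. Such a difference is plausible here: only one arm is asked to complete a training of about 2.5 hours, the intervention is meant to strengthen a public non-smoker identity, and participants know which arm they are in. Under the rule as written, the one analysis that could address this is run only if a comparison that cannot detect the problem is read as detecting it.

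**Working it through.** **1. The plan's own figure.** Inputs from the power section: control rate 0.25, difference 0.10 (so 0.35), 80% power, no continuity correction, 30% dropout. Two-sided alpha of 0.05 is my assumption; the article does not state it.

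n per arm = [1.96·√(2·0.30·0.70) + 0.842·√(0.25·0.75 + 0.35·0.65)]² / 0.10² = 329 after rounding up. Then 2·329/0.70 = 658/0.70 = 940, which matches the stated size. The calculation counts 658 people with an outcome and leaves 282 without one.

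**2. Can the baseline comparison detect MNAR?** Take true abstinence of 25%, and dropout of 12% in abstainers and 36% in smokers (assumed). Overall dropout is 0.25·0.12 + 0.75·0.36 = 30%. Responders show 0.25·0.88 / (0.25·0.88 + 0.75·0.64) = 0.22/0.70 = 31.4%. In 4,000 simulated trials of 940, with one baseline covariate unrelated to outcome, the dropout-completer test was significant in 5.1% of runs under this MNAR mechanism and in 5.0% under MCAR. If instead a covariate does predict smoking, a baseline difference will tend to appear, but MAR dropout that depends on that covariate would produce one too. Neither result separates MAR from MNAR.

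**3. What the ignorable branch analyses.** A logistic regression for a single time point contains no other outcome through which a non-responder could contribute. Using all available data therefore comes down to participants with that outcome, plus covariates.

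**4. What imputation adds.** At the planned 30% the 10% rule will be met. The article states no MNAR assumption for the imputation, and the standard form is MAR. If imputed by arm without informative post-baseline predictors, missing values are filled at about the responders' rate in the same arm, which returns the complete-case answer.

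**5. Possible size (all response rates assumed).** Observed rate = p·a / [p·a + (1−p)·r], where p is true abstinence, a the response rate of abstainers and r that of relapsers; 470 per arm; no true effect.

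| p (both arms) | a | r, control v intervention | Observed, control v intervention | Spurious gain | False positives |
|---|---|---|---|---|---|
| 35% | 85% | 60% v 50% | 43.3% v 47.8% | 4.5 points | about 20% |
| 25% | 85% | 70% v 60% | 28.8% v 32.1% | 3.3 points | about 15% |
| 25% | 85% | 62% v 58% | 31.4% v 32.8% | 1.5 points | 6.7% |

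Row 1 in full: control 0.2975/(0.2975 + 0.39) = 0.433; intervention 0.2975/(0.2975 + 0.325) = 0.478. Those analysed number 470·0.6875 = 323 and 470·0.6225 = 293. The pooled rate is 0.454, the standard error 0.0402, and the shift 0.0452/0.0402 = 1.12 standard errors, so the two-sided 5% test rejects in about 20% of trials.

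**6. Same response pattern in both arms.** With a = 85% and r = 60% in each arm, true rates of 25% v 35% are observed as 32.1% v 43.3%. The odds ratio is 1.615 both times. The absolute rates are overstated by about 7 and 8 points, and the difference reads 11.2 points where the truth is 10.

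**7. Would an unconditional check help?** In row 1, counting the missing as smoking gives 0.35·0.85 = 29.75% in both arms, so the spurious gain disappears. That holds because abstainers respond equally in the two arms; it is not general. A range of arm-specific shifts is therefore needed beside it.

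**The case against.** The plan is not without safeguards. Imputation is all but certain at 30% missing and brings non-responders back into an analysis. Covariates associated with dropout are adjusted for. Pattern mixture models are named. Smoking is also reported by text, weekly and then biweekly, and feeds Cox and Kaplan-Meier analyses of time to first relapse, where someone who reports relapse by text and later skips the 12-month survey can still count as an event. The false-positive figures need an arm difference in relapsers' response whose size and direction no document supports; the reverse pattern would bias against the intervention. The detail of sensitivity analyses and imputation variables commonly sits in an analysis plan that is not shown here.

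Most of this stands and limits the point. It does not rescue the rule. Covariate adjustment handles measured predictors only, standard imputation is MAR, and censoring in the relapse analysis may itself be informative. The decision rule is written in the article, so it is a wrong statement and not an omitted detail.

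A reader might also infer that about a third of participants have been lost, from "337 participants (65%) had completed the study with the 12-month follow-up surveys". The documents do not support that. The denominator is not given: 337/0.65 is about 518, whereas 337/940 is 36%. The figure is interim, and 6-month loss is not reported. The planned 30% is the firm number.

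**Conclusion.** Wrong as written, and should be fixed before analysis. Baseline characteristics cannot establish or exclude MNAR, so the article conditions its only MNAR method on a test that cannot trigger it, and no MNAR check on the 6- and 12-month primary outcome is assured. This rests on the article's text and needs no assumption about response rates. That the ignorable branch uses responders only is my inference from the separate model per time point, not the article's wording; the sample size arithmetic fits it.

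The size is conditional. Across the assumed cases above, the spurious gain runs from 1.5 to 4.5 points against a 10-point target, with false positives from 6.7% to about 20%. If non-response depends on smoking equally in both arms, the odds ratio is unbiased and only the reported abstinence rates are too high. Two stronger readings are tempting and go too far: that no planned analysis could show a problem, and that the trial's false-positive rate is 20%. The imputation and the text-based relapse analyses answer the first; the second is an illustration only.

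**What to change.** - Delete the rule that the baseline comparison decides ignorability. Keep the comparison as description and as a guide to covariates.
- Pre-specify, whatever that comparison shows and whatever the missing rate, an MNAR sensitivity analysis of the 6- and 12-month primary outcome in all 940 randomised participants. One option is a delta-adjusted pattern-mixture or tipping-point analysis with shifts that may differ by arm, reported alongside missing counted as smoking.
- Include the weekly and biweekly text smoking reports and the other survey waves in the imputation model. They record smoking before dropout and make MAR more credible.

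The cost is a change of wording and some extra analysis. The data are already being collected, and follow-up was still running when the article was submitted, so the change can be made before outcomes are analysed.
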